# Liuzijue Qigong vs traditional breathing training for patients with post-stroke dysarthria complicated with abnormal respiratory control: study protocol of a single center randomized controlled trial

**DOI:** 10.1186/s13063-018-2734-0

**Published:** 2018-06-26

**Keywords:** Dysarthria, Post-stroke, Abnormal breathing control, Six character formula, *Liuzijue qigong* (*LQG*)

## Abstract

**Background:**

Stroke-induced dysarthria is caused by muscle weakness, sacral or muscular dystonia, and incoordination of the articulatory organ formed by organic lesions caused by cerebral vascular obstruction or sudden bursting of blood vessels in the brain, which may cause abnormal breathing patterns, pronunciation, resonance, rhythm, and unclear articulation.

The Six Character Formula, or *Liuzijue qigong* (*LQG*), is an essential part of Chinese traditional exercises and focuses on breathing–speech synchronization. The purpose of the present study was to compare the effects of *LQG* with traditional breathing training (combined with basic articulation training in both groups) in patients with post-stroke dysarthria.

**Methods/design:**

The proposed study will be a single-center randomized controlled trial. A total of 100 patients, with a modified Frenchay Dysarthria Assessment (FDA) dysarthria assessment score < 27 and with a FDA speech breathing level ≥ b will be randomly divided into study (*LQG*, *n* = 50) and control (conventional breathing training, n = 50) groups. Basic articulation training will be conducted once a day, five times a week for 3 weeks. Data collection will be conducted at baseline, 1 week, and 2 weeks post-treatment initiation and after completion of the treatment (3 weeks). Comprehensive analyses will be conducted to measure and compare any differences in speech breathing dysfunction levels, comprehensive evaluation of dysarthria, maximum phonation time (MPT), maximal counting ability, signal-noise (S/Z) ratio, and loudness scales between the study and control groups.

**Discussion:**

This trial will provide evidence about the effectiveness of *LQG* for improvement of speech breathing function and speech ability in patients with post-stroke dysarthria complicated with abnormal breathing.

**Trial registration:**

Chinese Clinical Trial Registry, ChiCTR-INR-16010215. Registered 21 December 2016.

**Electronic supplementary material:**

The online version of this article (10.1186/s13063-018-2734-0) contains supplementary material, which is available to authorized users.

## Background

Dysarthria is a motor speech disorder caused by weakness, paralysis, or a lack of coordination of the motor-speech system [1]. It has been estimated that in the US 795,000 people will experience a new or recurrent stroke in 2013 [2] and 36–57% of individuals will have post-stroke dysarthria [3], which is often characterized by slurred, slow, breathless, or imprecise speech [4]. Individuals with post-stroke dysarthria often have problems forming understandable conversations [5] leading to emotional problems with social participation [6]. The recovery of post-stroke dysarthria is dependent on the improvement of breath control ability since the basis of sound is supported by the volume and control of respiratory airflow [7]. Intensive voice treatment, such as Lee Silverman voice treatment (LSVT) [8], has shown improved articulation, facial expression, and swallowing in patients with Parkinson’s disease (PD) [9] and some positive effects in other neurological disorders (stroke and cerebral palsy) [10]. Although non-speech oro-motor exercises (NSOMExs) are used in speech and language therapies for neurological disorders, especially stroke and other dysarthria classes, results on speech outcomes affected by NSOMExs have been inconclusive [11, 12]. The fact that post-stroke individuals often experience dysarthria complicated with abnormal breath control highlights the need to form a proper and efficient pattern of coordination between breath and speech, which is more likely to benefit patient coordination and help restoration of normal speech [13]. To date, traditional breathing training programs, such as blowing paper, candles, and ink and other exercises, deliberately force thoracic breathing into the abdominal breathing mode but ignore the synchronous treatment of pronunciation and breathing, blindly strengthening muscle strength, which makes the treatment program rigid.

The Six Character Formula, or *Liuzijue qigong* (*LQG*), is one of the New Health Exercise Series compiled by the China Qigong Management Center [14]. *LQG* has deep roots in traditional Chinese medicine and is a typical speech–breath therapy, which involves diaphragmatic breathing practice combined with the chanting of six different sounds (Xu, He, Hu, Si, Chui, Xi). The method is to inhale through the nose and then exhale through one of the six different tongue and mouth shapes, and also comply with appropriate body movements and mind-control breathing top-down or vice versa.

Recent studies have shown that *LQG* promoted functional lung capacity and improved the quality of life in older adults with chronic obstructive pulmonary disease (COPD) [15] and also influenced heart rate variability (HRV) in different postures [16]. It has also been demonstrated that a Health QiGong program, in which Xu and Xi exercises from *LQG* were included, could reduce the symptoms of PD and improve the body functions of PD patients [17]. Since *LQG* synchronizes breathing and speech and increases respiratory muscle strength and coordination, we hypothesize that it might help patients with post-stroke dysarthria, complicated by abnormal breathing control, to improve stability and the utilization efficiency of flow to establish normal breathing patterns for speech. Therefore, the aim of this study will be to investigate the therapeutic effect of the Six Character Formula in patients with post-stroke dysarthria complicated with abnormal respiratory control compared with traditional breathing training.

## Methods and design

### Trial design

Our proposed study is a single-center randomized controlled trial comparing the therapeutic effect of two breathing training methods (Six Character Formula vs traditional breathing training) in patients with post-stroke dysarthria complicated with abnormal respiratory control. The study design is depicted in the flow diagram shown in Fig. 1. The research protocol has been designed according to the SPIRIT recommendations (Fig. 2 and Additional File 1)

**Fig. 1 Fig1:**
[figure not shown]
Flow diagram of the study. Pulmonary function during speech will be tested and graded according to the FDA [25]: a--No difficulty; b--Inhalation or exhalation not smooth or is shallow; c--Marked interruptions of inhalation or exhalation, or difficulty of inhaling deeply; d--little control rate of inspiration or expiration- short of breath may appear. More consistently impaired than c; e--Patient unable to attempt task. No control

**Fig. 2 Fig2:**
[figure not shown]
SPIRIT figure of the Liuzijue Qigong study protocol

### Primary and secondary objectives of the study

In this study, we selected the “speech breathing level of a modified Frenchay Dysarthria Assessment (FDA)” as the primary objective indicator. At the same time, the curative effect will be assessed as complete response (CR), partial response (PR), and no response (NR) to assess statistically the effectiveness before and after treatment. The indicator will be ranked data, and the statistical method to be adopted is shown in Additional file 2: Table S1.

The study will also select modified FDA, maximum phonation time (MPT), maximal counting ability (MCA), signal-to-noise (S/Z ratio), and loudness level as secondary objective indicators. The data obtained from these indicators will be measurement data and data from the loudness level will be ranked data.

### Primary outcome measurement procedures

Outcome data will be collected at baseline, 1 week, and 2 weeks after the initiation of treatment, and also after the completion of the treatment (third week), by experienced physicians.

The primary measurement will be the speech breathing level of the modified FDA (Table 1).

**Table 1 Tab1:** Specific measurement of speech breathing level assessed by modified FDA

	Baseline	1 week	2 weeks	3 weeks
Speech breathing specific measurement				
Evaluation date				
Signature of therapist				

Speech breathing will be evaluated by letting the patients count to 20 as fast as possible in one breath. They will be assured not to be concerned about the articulation and just the number of breaths necessary to complete the task will be monitored. The normal outcome for this task is the performance in one breath.

The level of speech breathing-specific measurements will be defined as: a) normal and the number of breaths used as the baseline to quantify the seriousness of speech breathing dysfunction; b) the patient needs one additional deep-breath to smooth the speech; c) patient needs four deep breaths due to the disappearance of voice; d) patient needs seven deep breaths due to obvious variability of speech; e) patient spells one word with one breath due to serious impairment of speech. Subjects will be given a score of 1 for grade a, 2 for grade b, 3 for grade c, 4 for grade d, and 5 for grade e. The primary indicator will be the breath assessment of FDA.

The curative effect will be assessed as: 1) CR if the original level degrades ≥ 2 or reduces to the level of grade a; 2) PR if the original level degrades by 1; and 3) NR if the original level does not change or increases.

### Secondary outcome measurement procedures

The secondary outcome measurements will include the comprehensive evaluation of dysarthria using modified FDA, MPT, MCA, S/Z ratio, and a loudness scale (Table 2) at baseline, 1 week, and 2 weeks post-treatment initiation and after completion of treatment (third week) by experienced physicians.

**Table 2 Tab2:** Comprehensive evaluation of dysarthria using modified FDA, maximal counting ability, signal-to-noise (S/Z) ratio and loudness scale

	Baseline	1 week	2 weeks	3 weeks
Comprehensive evaluation of dysarthria				
Maximum phonation time (s)				
Maximal counting ability (s)				
S/Z ratio				
Loudness scale				
Evaluation date				
Signature of therapist				

The comprehensive evaluation of dysarthria using a modified FDA is composed of eight major items (including reflex, respiration, lips, tongue, jaw, palate, larynx, and speech) and 28 sub-items. Each item and sub-item will be divided into five scales (from a to e) according to the level of impairment and “scale a” is used as the baseline to quantify the recovery of dysarthria; a higher “a” score means good recovery from dysarthria.

Maximum phonation time (MPT) will be measured for the longest time that a patient can pronounce the simple vowel *a* after deep breathing. Measurement of MPT should satisfy the following requirements: 1) duration of pronunciation as long as possible; 2) even breath flow; 3) even breath loudness; and 4) tone within correct frequency range. The relatively longer MPT value will be selected as the final outcome from two measurements, which meet the above-mentioned requirements (vide supra). The tone and loudness of pronunciation need to be kept at a comfortable level. The maximal counting ability (MCA) will be defined as the longest time that a patient can pronounce the letter “E” (one in Chinese) without a break after a deep inhalation. The S/Z ratio is the ratio of the longest time that a patient can pronounce *s* vs *z* after a deep breath in. The loudness scale will be determined by a therapist while talking with a patient and graded as whispered, soft, conversational, loud, or shouting.

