#### Other key points

A patient with dysarthria after a stroke may have varying degrees of limb hemiplegia and abnormal posture and be unable to sit or stand. Therefore, it is often impossible to complete the action guidance of Liuzijue independently and accurately. Thus, the training position and guide actions cannot be made too rigid. Patients can take an alternative standing, sitting position, etc. A healthy upper limb can drive the affected upper extremity, or the therapist will stand next to the patient to help them complete the action to maintain the normal position of the thorax, spine, and pelvis and to provide a stable mechanical structure. With improvement in the patient’s ability to balance in the standing position, the training position will be gradually transitioned from the sitting position to an independent standing position. With improvement of the upper and trunk functions of the patient, the therapist will gradually reduce the amount of aid. Whether it is active or auxiliary, body movements are based on the principle of mild gentle restfulness. The goal will be to complete the accurate breath guidance protocol.

In addition, the therapist will measure the patient’s decibels before practicing the Six Character Formula and assist them to accomplish target decibel values with increased articulation and respiratory flow.

Basic articulation training will be conducted after training in both the study and control group, consisting of movement training (lips, tongue, and jaws) and pronunciation training from easy to difficult.

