### Statistical analysis

In the study, the main indicator, “speech breathing level according to modified Frenchay Dysarthria Assessment (FDA)”, will be ranked data. The statistical method will be as follows. (1) The main indicator will be compared between baseline and follow-up time with a signed rank test. The score change will be compared between groups using a rank-sum test. Unless indicated otherwise, hypothesis testing will use a two-sided test with *P* = 0.05 as the statistical cutoff point. (2) The influence of rehabilitation intervention time, stroke classification, age, and gender on the efficacy of the intervention method and the relative size of the efficacy will be estimated using a stepwise logistic regression model. (3) The overall efficacy evaluation will be the effective rate. The formula will be: Effective rate = (Excellent + Effective)/Total number of cases × 100%. A chi-squared test will be used to compare any differences in efficacy between the two groups.

The secondary outcomes will be analyzed using a repeated measure covariance analysis with the outcome baseline adjusted for as a covariate. We will test whether there is a statistically significant difference between the groups using a parameter representing treatment allocation. The ‘loudness level’ outcome is ranked data and will be analyzed in a similar way to the primary outcome.

The per-protocol (PP) population will include the randomized patients of the intention to treat (ITT) population but exclude those for whom the inclusion or exclusion criteria were not met and those who did not receive the actual treatments to which the patients were randomly allocated [18]. If the statistical results of the ITT and PP population data are the same, the results will be deemed to be reliable; if they are contrary, we intend to adopt the results of the ITT population. The method of processing missing data will be the last observation carried forward (LOCF). This refers to assigning the last observed value of the end point indicator to the subsequent missing evaluation point; that is, the last observation response will be considered to be the study end point.

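### Loudness is graded by volume with conversational speech in the middle, but is tested by rank change like the primary outcome, which cannot tell recovery from overshoot

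*Protocol article*

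**What the plan says.** All references are to the protocol article.

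- **Scale.** Under Secondary outcome measurement procedures, "The loudness scale will be determined by a therapist while talking with a patient", and speech is "graded as whispered, soft, conversational, loud, or shouting". The grades carry no numeric scores, none is named as normal, and neither end is named as favourable.
- **Data type.** Under Primary and secondary objectives of the study, "data from the loudness level will be ranked data".
- **Analysis.** Under Statistical analysis, the loudness "outcome is ranked data and will be analyzed in a similar way to the primary outcome". For the primary outcome that section says "The main indicator will be compared between baseline and follow-up time with a signed rank test" and "The score change will be compared between groups using a rank-sum test". Tests are two-sided at 0.05.
- **The scale being imitated.** Under Primary outcome measurement procedures, "Subjects will be given a score of 1 for grade a, 2 for grade b, 3 for grade c, 4 for grade d". The last grade scores 5. Grade a is normal and grade e is the most impaired, so a lower score is always better.
- **Training.** Under Other key points, within the study-group description, the therapist measures decibels before the LQG practice and will "assist them to accomplish target decibel values with increased articulation and respiratory flow". The Control group section and the description of the articulation training given to both arms contain no such step.

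**The concern.** A rank test of change fits the primary scale because every step along it means the same thing: less impairment or more. The loudness list lacks that property. It is ordered by volume, and the level of ordinary conversation is the third of five grades. Whichever end is called favourable, a middle grade can never rank best.

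A significant loudness result would therefore be hard to read. It could mean that more patients in one arm recovered from soft to conversational speech. It could equally mean that more of them went past it. In a trial report, a positive between-group test on this outcome would naturally be presented as a benefit, even where fewer patients in that arm speak at conversational loudness.

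**Working it through.** **Inputs.** The grade order and the tests come from the article. So does the size of 50 per arm (Sample-size calculation), which falls to 50 × 0.82 = 41 after the anticipated 18% loss. The article gives no loudness distribution and no planned effect on loudness, so there is no figure to reproduce. Every distribution below is an assumption. Taking conversational as the reference level is also an assumption, since the article names none.

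**Step 1: what the change score does.** Code the grades 1 to 5 in the listed order.

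- Soft to conversational: 3 − 2 = +1.
- Conversational to loud: 4 − 3 = +1.
- From soft, ending at conversational gives +1, loud +2 and shouting +3.

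Recovery and overshoot earn the same step, and overshoot ranks beyond recovery. Reversing the codes changes the signs but leaves conversational in the middle.

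**Step 2: a small example by hand.** All patients start at soft, 50 per arm. Arm A ends with 35 conversational, 10 loud and 5 shouting. Arm B ends with 45 conversational and 5 soft.

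- Chance that A ranks above B on change, ties counted half: 0.30 × 1 + 0.70 × (0.10 + 0.5 × 0.90) = 0.300 + 0.385 = 0.685. Two-sided rank-sum p is about 5 × 10⁻⁶.
- Chance that A is farther from conversational (distance 0, 1, 2): 0.10 × 1 + 0.20 × (0.90 + 0.5 × 0.10) + 0.70 × (0.5 × 0.90) = 0.100 + 0.190 + 0.315 = 0.605. Two-sided p is about 0.009.

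The same data show A significantly louder and also significantly farther from conversational speech.

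**Step 3: how often this could happen.** Simulated trials, 50 per arm, all starting at soft. The control arm ends, from whispered to shouting, at 5/35/55/4/1%. Mean distance from conversational in control is 2 × 0.05 + 0.35 + 0.04 + 2 × 0.01 = 0.51.

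| Assumed LQG end distribution | Beyond conversational | At conversational, LQG vs control | Mean distance, LQG | Rank-sum of change favours the louder LQG arm |
|---|---|---|---|---|
| 5/30/55/9/1% (almost no overshoot) | 10% | 55% vs 55% | 0.51 | about 10 to 11% |
| 5/30/45/18/2% (mild) | 20% | 45% vs 55% | 0.62 | about 25% |
| 5/25/35/30/5% (marked) | 35% | 35% vs 55% | 0.75 | about 70% |

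With no difference between arms, a two-sided 0.05 test would favour LQG in about 2.5% of trials. With 41 per arm, the marked case gives about 63%.

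In the marked case the chance that an LQG patient ranks above a control patient is 0.05 × 0.025 + 0.25 × 0.225 + 0.35 × 0.675 + 0.30 × 0.97 + 0.05 × 0.995 = 0.6345. The distance score finds LQG significantly farther from conversational in about 52% of the same trials.

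**Step 4: removing the genuine gain.** In all three rows LQG also has fewer soft patients than control, so part of the signal is real recovery. Holding whispered and soft equal at 5% and 35%, overshoot of 15% against 5% gives about 8% of trials in favour of LQG, and 25% against 5% gives about 19%.

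**The case against.** The strongest reply is that volume is a proper ordinal quantity and the planned test validly asks whether one arm became louder. If most patients lie between whispered and conversational, which is plausible for breathless speech after stroke, the scale is in practice monotone and the test serves well. Nothing in the article suggests that many patients would reach shouting while talking with a therapist. This stands as a limit on size. It does not remove the fault, because the plan fixes a method that is sound only if overshoot is rare and does not say so.

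A second reply is that scores and direction are commonly left to a full protocol or analysis plan, which is not shown. That is right as regards coding, and the missing codes alone would be no finding. The choice of method, however, is stated, and no monotone coding of the five grades repairs it.

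Two stronger readings are tempting, and the article supports neither:

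- **Shouting counts as the best result.** No section says so. The test is two-sided and has no built-in direction. Copying the primary coding literally, with the first grade best, would make whispered the best.
- **The decibel coaching pushes LQG patients past conversational.** The target values are not given and could be conversational. Coaching may also be an intended part of the LQG package, which a trial may legitimately compare as a whole.

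Finally, the 70% figure depends on an assumed 35% of LQG patients ending beyond conversational, so it should be read only as the top of the range shown.

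**Conclusion.** The point holds as a misfit between scale and test. The article borrows an analysis built for a scale with one good end and applies it to a scale whose ordinary level lies in the middle, without naming a normal grade or a favourable direction. A significant difference would then show that one arm is louder, not that it speaks closer to conversational level.

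The size cannot be taken from the article. Across the three simulated scenarios with 50 per arm, the share of trials favouring the louder arm runs from about 10 to 11% to about 70%. It is about 8 to 19% when the two arms do not differ in soft or whispered speech. These figures assume that all patients start at soft and that conversational is the reference.

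Severity is minor. One secondary outcome is affected. The primary outcome and the sample size are not.

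**What to change.** Before the data are analysed, state which loudness grade is the reference. If it is conversational, as assumed here, do one of the following:

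1. Recode loudness as distance from it (conversational 0, soft or loud 1, whispered or shouting 2) and apply the planned tests to that score and its change.
2. Compare the proportion of patients at conversational between arms.

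Show the raw five-grade table by arm and visit beside the result.

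Add one sentence on interpretation: decibel measurement and coaching to a target are described for the LQG arm alone, so a loudness difference is not by itself evidence of better breathing control.

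The cost is a change of wording and a recode of ratings already planned, with no new data collection. The downside is that the distance score merges too soft with too loud, which is why the raw table should accompany it.
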